## Abstract

**Supplementary Information:**

The online version contains supplementary material available at https://doi.org/10.1007/s00277-026-07290-9.

## Introduction

Cellular therapies like allogeneic hematopoietic cell transplantation (alloHCT) and chimeric antigen receptor T (CAR T)-cell therapy have led to an improvement in prognosis of patients with hematologic diseases [1, 2]. AlloHCT has been established over the past decades as a standard treatment for various hematological diseases [2]. Since 2018, CAR T-cell therapy has been approved for patients with lymphoma and certain types of leukemia in Germany [3, 4]. Both alloHCT and CAR T-cell therapy require a high level of expertise, specific structural requirements such as the accreditation of treatment centers, and substantial personnel resources for the primary hospital stay and post-treatment care [5, 6]. In Germany, regulatory and administrative requirements are governed by a decision of the Federal Joint Committee (Gemeinsamer Bundesausschuss, G-BA) [7].

The continuous increase in the number of patients treated with innovative cellular therapies has led to a growing population requiring post-treatment care [2]. After discharge from the primary hospital stay for cellular therapy, patients undergoing these innovative treatments remain at high risk of mortality and severe complications, including life-threatening infections, organ toxicities, and disease relapse following cellular therapy in general, as well as graft-versus-host disease (GvHD) after alloHCT and cytokine release syndrome (CRS), or neurotoxicity, such as immune effector cell-associated neurotoxicity syndrome (ICANS), after CAR T-cell therapy, in particular. In a large Japanese trial among alloHCT recipients, 2-year non-relapse mortality (NRM) was reported to be 16% [8]. Within a large US-American cohort, 31% of patients required readmission within the first 100 days after alloHCT [9]. Within a German cohort rehospitalizations after alloHCT were as high as 55% [10]. NRM in CAR T-cell therapy was reported to be disease-specific, e.g., reaching 10.6% in mantle cell lymphoma patients [11]. 41% of CAR T-cell therapy patients needed rehospitalization within an US-American cohort with 9% intensive care unit readmissions [12].

Due to their complexity and in view of stringent quality assurance measures, alloHCT and CAR T-cell therapy are performed in certified treatment centers [7]. Post-treatment care is challenged by the necessity for many patients, particularly those residing in rural areas of Germany, to travel significant distances (up to 200 km) to attend regular outpatient appointments or to access the cell therapy center in the event of complications possibly resulting in significant financial and physical stress for patients and their healthcare providers [13]. Furthermore, hours spent in waiting rooms and taxis could be a source of infection in a highly susceptible population.

In a previous study conducted in Boston, Massachusetts, USA, shared post-treatment care between the cell therapy center and community-based physicians after alloHCT was found to be safe, and resulted in non-inferior early NRM and improvement of short-term quality of life (QoL) at day 100; however, no long-term QoL benefit was observed at six months [14]. In Germany, structured post-treatment care programs for patients after cellular therapy currently neither exist nor receive funding from statutory health insurance.

In preparation to design this study protocol, a structured exchange was conducted with patient advocates and cell therapy centers planning to participate in the study. This exchange revealed substantial heterogeneity in post-treatment care across centers and physicians, as well as limited collaboration between healthcare sectors, e.g., hematologists at the cell therapy center, community-based hematologists, and general practitioners.

## Methods

Based on these challenges, we developed the SPIZ program (cross-sector care for patients with hematological diseases following innovative cell therapy, German: Sektorenübergreifende Versorgung von Patientinnen und Patienten mit hämatologischen Erkrankungen nach innovativer Zelltherapie) as a multidisciplinary collaboration of hematologists, nursing scientists, health services researchers, computer scientists, and patient advocates, comprising the following components (Fig. 1):

**Fig. 1 Fig1:**
[figure not shown]
Components of the SPIZ program: By integrating case managers and onco nurses, additional personnel resources are mobilized as part of a specialized care team. Case managers serve as the primary point of contact and as coordinators along the care pathway, whereas onco nurses provide advanced clinical support through home visits and nursing consultations. The psycho-oncology and social counseling services offer psychological support and help to navigate social and legal complexities. App-based telemonitoring via the SMILe system and video consultations constitute digital components of the SPIZ program. Regular case conferences with community-based hematologists facilitate cross-sectoral coordination of care. Onco nurse: oncology nurse; SMILe: SteM-cell-transplantatIon faciLitated by eHealth, SPIZ: cross-sector care for patients with hematological diseases following innovative cell therapy

Case Managers serve as the primary contacts for patients and their families, as well as for community-based hematologists and general practitioners. They organize and coordinate diagnostic and follow-up appointments, facilitate communication across healthcare sectors (e.g., between inpatient and outpatient healthcare providers), and arrange virtual case conferences with community-based hematologists. In addition, case managers provide technical support for the use of the program’s digital components. The SMILe App (SteM-cell-transplantatIon faciLitated by eHealth) enables patients to document vital parameters and relevant clinical symptoms on a daily basis. In addition, patients may use a free-text comment field within the app to request a callback. SMILe Care provides the interface for oncology nurses (onco nurses) to conduct continuous symptom telemonitoring [15].Onco nurses monitor patient-reported data entered in the app using a specialized application (SMILe Care) and present it to the treating hematologist in the event of abnormalities. They conduct regular home visits to assess patients’ health status, collect blood samples, and evaluate the home environment, for example with regard to hygiene standards and the need for supportive care aids. These home visits partially replace routine post-treatment care visits at the hospital.The psycho-oncology service provides specialized psychological support to facilitate patients’ coping with illness and the emotional processing of their experiences. The social counseling service offers professional assistance in addressing personal and social challenges. Contact with both services is typically established during the initial inpatient stay and is maintained to ensure continuous, needs-based support throughout the SPIZ program.Video consultations with the responsible hematologist at the cell therapy center are conducted to complement in-person and home-based care and to ensure continuous specialist involvement. These consultations are typically scheduled following a home visit by an onco nurse but may also be arranged on short notice to provide additional telemedical support whenever clinically indicated.Fortnightly online case conferences are held to discuss patients’ post-treatment care plans within an interdisciplinary, multiprofessional setting by hematologists from the cell therapy centers, community-based hematologists, professionals from psycho-oncology and social counseling services, as well as SPIZ case managers and onco nurses. These conferences aim to ensure coordinated, comprehensive care and to prevent loss of information across care sectors.

Case managers and onco nurses are registered nurses who have completed a three-year professional nursing program and specialist training in oncology or an equivalent qualification. Certification in case management, or a commitment to obtain such certification, is also required for the case management role. Before assuming study-related responsibilities, staff receives project-specific training covering the study procedures, use of the SMILe App and monitoring dashboard, standardized assessments, documentation requirements, and escalation procedures. The average caseload is 25 subjects in the intervention group over the whole study period per full-time-equivalent. Staff works within multidisciplinary teams comprising case managers, onco nurses, physicians, and the project coordinator. Organizational oversight is provided by the project coordinator, while clinical supervision and clinical decision-making remains the responsibility of the hematologists at the respective center.

The effectiveness of SPIZ is currently being evaluated in a randomized controlled trial (RCT) conducted in accordance with study protocol version 5 (dated November 17, 2023): In the intervention group, patients receive the measures described above, while the control group undergoes post-treatment care according to institutional standards. During the early post-cellular therapy period (day 30 to day 100), care is particularly intensive and varies between patients depending on individual needs. After approximately day 100, the intensity of medical and nursing contacts decreases according to the individual clinical trajectory in both the intervention and control arms.

To ensure coverage of a large service area with substantial rural representation, the SPIZ program is implemented at all three cell therapy centers in the federal state of Saxony, Germany: University Hospital Dresden, University Hospital Leipzig, and Klinikum Chemnitz. Structured post-treatment care plans were implemented to standardize and coordinate patient care (supplementary Figs. 1 and 2).

### Eligibility criteria

The target population comprises all adult patients (≥ 18 years) after alloHCT or CAR T-cell therapy.

#### The primary study population are patients who

have been treated at one of the three cell therapy centers in the federal state of Saxony,reside within the regular service area (≤ 200 km) of one of the three centers,own a smartphone and are able to use it,have provided written informed consent to participate in the SPIZ RCT, including all components of the intervention, and.are covered by the German statutory health insurance system.

##### Patients meeting the following **exclusion criteria** are not included to the SPIZ study

more than eight days have elapsed since hospital discharge following alloHCT or CAR T-cell therapy,insufficient German language proficiency to use the SMILe App and to complete study questionnaires (e.g., QoL or program satisfaction),medical conditions that render participation in an intensified outpatient post-treatment care pathway infeasible.

The secondary study population consists of patient advocates, and healthcare providers including hematologists, case managers and onco nurses at the three participating cell therapy centers as well as community-based hematologists, being involved in the SPIZ program.

### Technical implementation of digital elements

The SMILe App enables patients after alloHCT to systematically document their health status continuously and in real-time, including vital parameters and disease or cellular therapy associated symptoms. SMILe Care provides an interface enabling onco nurses to review these patient-reported outcomes [15, 16]. For the SPIZ program, the app was augmented with additional functionalities to address the specific medical needs of patients following CAR T-cell therapy. In addition, the integrated patient education lexicon was substantially expanded to include more comprehensive information regarding alloHCT and CAR T-cell therapy. Additionally, a secure text-based communication function enabling patients to contact the treating center was implemented. The app itself does not generate automated alerts or apply predefined alert thresholds or algorithms. Data entered into the app are generally reviewed by onco nurses on the morning of the next working day. Individual abnormal measurements and clinically relevant trends are assessed in accordance with the participating center’s standard operating procedures. If an abnormality is identified, the responsible physician at the respective center is contacted immediately to determine further management. If clinically indicated, the patient is subsequently contacted without delay and directed to an appropriate level of care, e.g. local emergency medical services, the patient’s outpatient hematologist or primary care physician, cellular therapy center hematologist or the emergency department.

The app is not intended for emergency communication and is not monitored continuously or outside the specified review periods. During onboarding, participants are explicitly instructed not to use the app for urgent concerns. During case management service hours (8 a.m. to 3 p.m.), urgent concerns are immediately escalated to the responsible physician. Outside these hours, participants are instructed to follow the established pathways of their treating center, including contacting its on-call service or, depending on the severity of the concern, contacting local emergency medical services or presenting to an emergency department. These instructions are consistent with the center-specific standard operating procedures and routine discharge information provided following cellular therapy.

Video consultations are conducted via institutional, secure virtual consultation platforms, e.g. CARY medical by Webex. Online interdisciplinary case conferences are held every two weeks and documented via a virtual tumor board platform.

### Enrollment, randomization and patient pathway

After enrollment, which takes place not later than eight days following discharge from the primary inpatient stay for cellular therapy, patients are randomly assigned in a 1:1 ratio to either the SPIZ program or the control group. The randomization is stratified according to patient age (< 60 years or ≥ 60 years) for each of the three cellular therapy centers individually using the REDCap (Research Electronic Data Capture)-based project database. Prior to the commencement of the study, age-group-specific randomization lists have been created through block randomization, employing permuted blocks of variable length. These randomization lists are prepared by the Dresden Coordination Center for Clinical Trials, which is also responsible for the preparation and administration of the REDCap project database. The randomization result is displayed to study staff in REDCap once informed consent and eligibility based on the inclusion and exclusion criteria have been documented. Depending on group allocation, patients proceed through either the SPIZ pathway or standard routine care (Fig. 2). Patients are scheduled to receive treatment for a minimum duration of 12 months and a maximum duration of 24 months.

**Fig. 2 Fig2:**
[figure not shown]
Patient pathway in the SPIZ RCT: After enrollment, patients are randomized in a 1:1 ratio to either the SPIZ group or the control group. In the SPIZ group, home visits by onco nurses are carried out as needed and alternate with routine outpatient clinic visits. Patients document vital signs and symptoms daily via the SMILe App, which are monitored by onco nurses. Regular video consultations with hematologists at the cell therapy center take place, either following home visits or on demand. Patients in the control group receive routine post-treatment care. Onco nurse: oncology nurse; R: randomization

Home visits by an onco nurse are scheduled at predefined time points (supplementary Figs. 1 and 2) and constitute a planned component of the intervention. Together with a subsequent video consultation, each scheduled home visit replaces a routine outpatient visit at the center. Additional home visits may be arranged when clinically indicated. Multidisciplinary case conferences are scheduled at week 6, week 12, month 6, month 12 and month 24 (supplementary Figs. 1 and 2).

Home visits by an onco nurse combined with video consultations replace some visits to the cell therapy center in comparison with standard of care. Besides that, participants in the intervention group continue to receive all routinely indicated outpatient visits, diagnostic assessments, treatments, and access to emergency care at their treating center. Additional home visits, video consultations, app-supported monitoring, case management, and multidisciplinary case conferences are supplementary components. Participants in the control group receive usual standard of care without the protocol-specific SPIZ components.

Missed app entries, unsuccessful attempts to contact a participant, and the outcome of each contact attempt are documented in the hospital information system and, separately, in the REDCap database. When app entries are missing, the case manager or onco nurse make repeated attempts to contact the participant. If the participant remains unreachable, the responsible physician is informed, and further action is taken in accordance with the respective center’s standard operating procedures.

### Hypotheses and outcomes

The primary hypothesis is that patients receiving the SPIZ intervention following cellular therapy (intervention group) experience better health outcomes in terms of lower mortality and fewer hospital readmissions than patients receiving routine clinical care (control group). The target population comprises all adult patients with hematologic diseases who undergo alloHCT or CAR T-cell therapy at one of the three participating centers.

Efficacy will be evaluated using a composite primary endpoint comprising mortality and disease-related rehospitalization. The latter is defined as unplanned rehospitalization due to complications typically associated with either the underlying hematologic disease (e.g., disease progression) or cellular therapy. Such complications include infections and organ toxicities following either therapy, GvHD following alloHCT, and CRS or neurotoxicity, such ICANS, following CAR T-cell therapy. The primary endpoint will be evaluated by confirmatory statistical analysis 12 months after cellular therapy.

Secondary hypotheses with corresponding outcomes and data sources are listed and described in Table 1.

**Table 1 Tab1:** Overview of the secondary hypotheses. The four secondary hypotheses to be examined are listed along with their corresponding secondary outcomes and the respective data sources or scales

Secondary hypotheses	Secondary outcomes	Data source / scale
a) SPIZ leads to improved longitudinal clinical outcomes	◼ Mortality ◼ Complications, e.g., infections, GvHD (alloHCT), CRS (CAR T-cell therapy), neurotoxicity (CAR T-cell therapy), relapse, and death assessed by incidence and duration (as feasible) ◼ Rates and duration of unplanned rehospitalizations ◼ Symptom burden, including nutrition, body weight, body temperature, skin changes, bowel habits, and neurological symptoms ◼ Laboratory values ◼ Therapy adjustments ◼ Conducted assessments, e.g. staging, pulmonary function testing, echocardiography	REDCap-based project database, SMILe system
b) SPIZ leads to improvements in QoL and patient empowerment	QoL assessed using established questionnaires	EORTC QLG Core Questionnaire QLQ-C30 and module for low-grade non-Hodgkin lymphoma QLQ-NHL-LG20 [17], NCCN Distress-Thermometer (German version) [18]
	Empowerment: ◼ Shared decision making ◼ Pathway adherence ◼ Self-assessment of health status ◼ Patients’ level of information about the course of treatment and possible treatment options	Questionnaire survey using self-developed items; Qualitative interviews with patients
c) SPIZ increases satisfaction among both patients and healthcare providers with a high level of acceptance	Patients’ perspective ◼ Satisfaction with the program and/or specific components ◼ Causes for satisfaction/dissatisfaction ◼ Suggestions for improvement of the SPIZ program	Questionnaire survey with modified PSCC (Patient Satisfaction with Cancer Care*)* [19] and self-developed items; Qualitative interviews with patients
	Healthcare providers’ perspective ◼ Satisfaction with the program and/or specific components ◼ Satisfaction with communication between different healthcare provider groups ◼ Causes of satisfaction/dissatisfaction	Qualitative interviews with healthcare providers
d) SPIZ is cost-effective from the perspective of the statutory health insurance system	◼ Rates and costs of rehospitalizations ◼ Costs of outpatient treatments and medication ◼ Travelling costs ◼ Level of care related and palliative care costs	REDCap-based project database, Statutory health insurance routine data from AOK PLUS

*alloHCT* allogeneic hematopoietic cell transplantation, *CAR* T-cell therapy, chimeric antigen receptor T-cell therapy, *GvHD* graft-versus-host disease, *QoL* Quality of Life, *REDCap* Research Electronic Data Capture, *SMILe* SteM-cell-transplantatIon faciLitated by eHealth, *SPIZ* cross-sector care for patients with hematological diseases following innovative cell therapy

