### Sample size

Sample size calculation for the primary study population is based on the primary endpoint. The literature available at the time of sample size planning showed that there was a rehospitalisation rate of 55% after alloHCT in a German population [10]. Given that deceased patients were typically hospitalised beforehand, it can be inferred that the 55% figure accurately represents the routine clinical care. The SPIZ program should reduce the mortality or disease-specific rehospitalisation rate to 35% or less. The case number calculation was performed with a one-sided Fisher test. Given a significance level of 5% and a yielded power of 80%, it is assumed that 143 patients in the intervention group and 143 patients in the control group are required (calculated with GPower 3.1). With an estimated drop-out rate of 5%, 302 patients must be included.

While disease- and cell therapy-specific rehospitalization or death includes all complications typically associated with the underlying hematological condition or cell therapy, other reasons for rehospitalization or death are defined as independent, e.g., joint replacement due to arthrosis, or an accident. The analysis of the primary endpoint will be conducted one year after primary hospital discharge of the last enrolled patient. Death or rehospitalization are considered equivalent primary endpoints.

Recruitment of health care providers involved in SPIZ (secondary study population) for twelve qualitative interviews starts 18 months after initiation of patient enrollment.

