## Discussion

The SPIZ study will evaluate a structured model of post-treatment care after alloHCT and CAR T-cell therapy in comparison with routine care in a multicenter RCT, thereby unlocking the potential of intensified support by specialized healthcare providers combined with digital components. Through telemonitoring, we aim to facilitate the early detection of complications and enable timely, targeted interventions and increase the QoL of the patient by reducing the timely intensive visits in the center. By providing additional personnel resources and conducting home visits, we aim to relieve the burden on patients who are often severely affected by their underlying disease and cellular therapy, without bypassing medically necessary visits to the cell therapy center. This approach has the potential to reduce travel burden for many patients, especially those living in rural areas, as it is true for cellular therapy patients in Saxony, with the potential of transferring it to other less densely populated states and countries. The option of short-notice video consultations will allow for rapid scheduling of minor follow-up appointments.

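### Whether a planned readmission counts toward the primary endpoint is stated differently in two sections, and planned status could differ by arm; state one rule and report planned disease-related stays before unblinding

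*Protocol article*

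**What the plan says.** The Hypotheses and outcomes section of the protocol article sets a "composite primary endpoint comprising mortality and disease-related rehospitalization". The readmission part is "defined as unplanned rehospitalization due to complications typically associated with either the underlying hematologic disease (e.g., disease progression) or cellular therapy". A stay must therefore meet two conditions: it is unplanned, and its cause is the disease or the cellular therapy. Disease progression is the section's own example of a qualifying cause.

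The Sample size section describes the endpoint again. It states that "disease- and cell therapy-specific rehospitalization or death includes all complications typically associated with the underlying hematological condition or cell therapy", and that "other reasons for rehospitalization or death are defined as independent, e.g., joint replacement due to arthrosis, or an accident". This sorts events by cause; planned or unplanned does not appear.

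Table 1 lists "Rates and duration of unplanned rehospitalizations" among the secondary outcomes. The article does not say what makes a stay unplanned. Under Data collection and management, all potential primary endpoint events go to two hematologists blinded to allocation, with a third if they cannot agree.

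On the programme itself, the Methods say of the case managers: "They organize and coordinate diagnostic and follow-up appointments, facilitate communication across healthcare sectors". The Discussion says of telemonitoring that "we aim to facilitate the early detection of complications and enable timely, targeted interventions".

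**The concern.** The sole confirmatory endpoint is described in two ways, and the difference affects an event that the article itself names. If progression is found and the patient is then admitted by appointment, the stay meets the cause condition and fails the unplanned condition.

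The second issue remains even if the first text governs. SPIZ adds daily symptom entries reviewed by nurses, home blood samples, short-notice video consultations and coordinated appointments, and controls receive none of these. If complications are recognised earlier, some stays that would have been emergencies may be arranged instead. Such a stay leaves the numerator although the patient was still admitted for the same cause. Blinded adjudicators cannot correct this, because the stay really was planned.

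At stake is the interpretation of a lower composite in the SPIZ arm. It could mean fewer deaths and complications needing admission, or partly a different route into hospital. As described, the analysis could not tell these apart.

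**Working it through.** **Comparison of the two texts**

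| Stay | Hypotheses and outcomes | Sample size |
|---|---|---|
| Emergency admission, infection after therapy | event | event |
| Scheduled admission, disease progression | no event | could be an event |
| Scheduled joint replacement for arthrosis | no event (planned, and other cause) | no event (other cause) |
| Accident | no event (other cause) | no event (other cause) |

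Only the second row differs. The joint replacement is typically elective and would not need a cause exclusion if planned stays were already out, which hints at a cause-only rule. The accident points the other way: it is unplanned, so a cause exclusion is needed under the two-condition rule as well. The examples do not settle the matter.

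**Size, as an illustration**

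The plan gives no figure for the share of disease- or therapy-related stays that are planned, so there is nothing of its own to reproduce here.

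Inputs from the article:
- 153 patients per arm (Results).
- Control event rate 55%, one-sided Fisher test, 5% level (Sample size). The analysis section names Fisher's exact test without a side; one-sided is taken from the planning.

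Assumptions:
- No true effect, so 55% in both arms.
- A net fraction r of SPIZ patients with an event lose event status because their qualifying stay was planned.
- No such loss in controls.

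SPIZ rate = 0.55 × (1 − r). Patients affected = 153 × 0.55 × r = 84.15 × r. The rejection probability is the exact sum, over all pairs of binomial counts, of the outcomes at which the one-sided Fisher p-value is at most 0.05.

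| r | Patients affected | SPIZ rate | Chance of a significant result |
|---|---|---|---|
| 0 | 0 | 55.0% | 3.7% |
| 1% | 0.8 | 54.45% | 4.6% |
| 2% | 1.7 | 53.9% | 5.6% |
| 5% | 4.2 | 52.25% | 9.8% |
| 10% | 8.4 | 49.5% | 20.9% |

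Two contrasting cases, computed the same way:
- The same 5%, 10% or 20% is lost in both arms: 3.7% to 3.8%, so no inflation.
- Closer monitoring adds a net 5% to SPIZ events (0.55 × 1.05 = 57.75%): 1.2%, so the bias runs against SPIZ.

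The fraction r is net. A patient leaves the numerator only by surviving to 12 months with no other qualifying unplanned stay. Deaths cannot be rescheduled, yet the formula applies r to all events, so a given r requires a larger share of the readmission-only patients to change status.

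**The case against.** The strongest reply is that the sections can be read together. Hypotheses and outcomes gives the definition, Table 1 also speaks of unplanned stays, and the Sample size sentence only explains which causes qualify. A reader might infer that the Sample size section counts every readmission caused by the disease or therapy, planned or not. It does not say so; it only leaves the word out. This stands, and it makes the two-condition definition the likelier operative rule.

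A reader might also infer that SPIZ is known to change how patients are admitted. The documents do not say that. Case managers arrange diagnostic and follow-up appointments, and admissions are not mentioned. After an abnormal app entry, the listed routes are emergency services, outpatient physicians, the center hematologist and the emergency department. SPIZ patients keep routine and emergency access, and closer monitoring could also produce more unplanned stays. The arm difference is therefore a plausible inference of unknown direction.

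Avoiding emergency admissions is a legitimate aim of the programme, and an endpoint of unplanned stays measures it. Replacing the endpoint with a cause-only rule after enrollment closed would be a debatable change, and the point does not require it.

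Finally, this is an article; the full protocol and SAP, which are not shown, may define *unplanned* in detail. That answers a complaint about missing detail. It does not answer two differing descriptions of the primary endpoint in one text.

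**Conclusion.** The point holds in a limited form. The two sections differ on whether planned status matters, and the difference decides how a scheduled admission for progression is classified. The unplanned condition is probably the intended one. Under it, planned status could plausibly differ between arms in a trial of monitoring and care coordination whose components go to one arm only, and blinded adjudication does not remove a real difference of that kind.

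The error rates should not be read as the trial's false-positive rate. They show what assumed one-sided net shifts would do: 3.7% with none, about 9.8% at 5% (some four patients) and about 20.9% at 10% (some eight). Shifts of 1% to 2% have little effect (4.6% to 5.6%), an equal shift in both arms has none, and a shift the other way works against SPIZ. What they do show is that a few patients per arm are enough to matter, which justifies collecting the information.

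**What to change.** Before unblinding:

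1. Give Hypotheses and outcomes and Sample size one identical rule for the readmission component, and give the blinded adjudicators that rule. The same edit should settle the neighbouring mismatch on deaths: the first section counts mortality without a limit on cause, while the second calls deaths from other causes independent.
2. If *unplanned* is kept, have the adjudicators also classify planned stays caused by the disease or the therapy, and report their number by arm.
3. Prespecify a sensitivity analysis of the 12-month composite that also counts those planned stays, excluding any already scheduled before randomization.

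This needs no new patients and uses the existing adjudicators. Enrollment closed in January 2026 and first results are expected in mid-2027, so there is time. The cost is some extra stays to adjudicate. The apparent effect may also be smaller in the sensitivity analysis, and the sponsor should accept that in advance.
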